## 10.2. Observation and Evaluation by Visit Schedule

### 10.2.1. Visit 1 (Screening Visit/Day -1 ~ Day 0)

#### 1) Obtaining Written Consent

- Before conducting any clinical trial procedures, the investigator must use the 'Informed Consent Form for Subjects' to explain the study title, purpose, duration, methods, expected benefits, risks, subject protection, and the right to voluntarily consent or withdraw. Sufficient time will be given for the subject to make a voluntary decision. Once the subject decides to participate, they will be asked to sign the form. A copy will be provided to the subject, and the original will be retained by the study site.
- A screening number will be assigned in the order that consent is obtained.

✓ KIOM\_2024\_CC\_GGTCS\_0X\_SOOO

#### 2) Demographic Survey

- The subject's initials (in English), sex, date of birth, age, history of alcohol use (whether they drink, amount of alcohol consumption), and smoking history (whether they smoke, amount of smoking) will be surveyed and recorded in the Case Report Form (CRF).

#### 3) Medical and Treatment History (Drug History) Survey

- The subject's medical history and drug administration history will be investigated in detail through interviews and a review of past medical records. The presence of a history of sinusitis, allergic rhinitis, pneumonia, influenza, COVID-19, bronchitis, otitis media, tonsillitis, chronic respiratory diseases (COPD, bronchial asthma, bronchiectasis, interstitial lung disease, other chronic respiratory diseases), malignant tumors, active infections, blood coagulation disorders, neuropsychiatric, hepatic, renal, cardiovascular, respiratory, endocrine, or central nervous system diseases will be checked. If a history of these diseases is present, the subject will be excluded.
- A medical history from within the past 3 years, including the diagnosis name, date of diagnosis, and whether it is ongoing at the time of screening, will be recorded in the CRF. Surgical history from within the past 3 years, including the name of the surgery and date, will also be recorded.

- Drug history will be investigated for medications taken within the last 3 months and those currently being taken at the time of screening. For prior/concomitant medications, the drug name (brand name), total daily dose, route of administration, start date, end date, whether it is ongoing, and purpose will be recorded.
- 4) Physical Examination
- Through a review of medical records and an interview, the investigator will examine the cardiovascular, peripheral vascular, skin/mucosa, eyes (excluding vision impairment), ENT, respiratory, musculoskeletal, endocrine, renal/genitourinary, neurological/psychiatric, oncological, infectious disease, and gastrointestinal/hepatic/biliary systems, as well as allergies and drug hypersensitivity reactions, and record whether they are normal or abnormal. If abnormal, a medical opinion will be recorded in the CRF, and suitability for participation in the clinical trial will be confirmed.
- 5) Vital Signs Measurement
- Vital signs including blood pressure (systolic, diastolic), pulse rate, and body temperature will be measured. Blood pressure and pulse rate will be measured using an automated sphygmomanometer while the subject is seated after resting for at least 3 minutes at every visit. Body temperature will be measured using an electronic thermometer after blood pressure is measured.
- 6) Physical Measurements
- The subject's height and weight will be measured and recorded via a body composition analysis.
- 7) Laboratory and Pregnancy Test
- The laboratory test items are as follows. For women of childbearing potential, a urine hCG test will be measured after an interview if there is any uncertainty about pregnancy status.
    - ✓ Complete blood count: RBC, WBC, Hemoglobin, Hematocrit, Platelet
    - ✓ Liver function test: AST, ALT, BUN, Creatinine, Glucose
  - The investigator may conduct additional tests related to any abnormal results.
- 8) EKG
- EKG will be performed to check for abnormal findings, and if any are present, the subject will be excluded. EKG results from within 2 weeks prior to obtaining consent are acceptable as screening results (when using test results from another institution, a results sheet that can confirm the findings must be secured.).
  - Investigator may conduct additional tests related to any abnormal results.
- 9) Chest, PNS (paranasal sinuses) X-ray

- Chest or PNS X-ray will be performed if the investigator deems a differential diagnosis necessary.
- Chest X-ray will be checked for findings suggestive of diseases that are part of the exclusion criteria, such as consolidation, atelectasis, emphysema, fibrosis, or a mass.
- PNS X-ray will be checked for findings suggestive of sinusitis, such as mucoperiosteal thickening, haziness, or air-fluid levels in the sinuses.

#### 10) Nasal Congestion Severity Score

- This is a 0-3 point scale used to assess the severity of nasal congestion symptoms, which subjects will self-evaluate (0=none, 1=mild, 2=moderate, 3=severe).
- It will be assessed at Visit 1.

#### 11) Pattern Identification for Common Cold Questionnaire

- It will be used to classify the subject's pattern type to see if there is an effect difference by pattern.
- It classifies the patterns as Wind-Cold type, Wind-Heat type, or other types.
- It will be assessed at Visit 1.

#### 12) Confirmation of Inclusion/Exclusion Criteria

- Only for subjects who have voluntarily signed the clinical trial consent form, final confirmation of eligibility based on the inclusion and exclusion criteria will be made at the screening visit using the demographic survey, medical and treatment history (drug history) survey, physical examination, vital signs measurement, laboratory tests, pregnancy test, Chest and PNS X-rays, and EKG. The final decision on suitability will be made by referencing the laboratory test results and recorded. The subject will then be notified by phone to inform them of the clinical trial schedule and precautions, and to set the date for the baseline visit.

### 10.2.2. Visit 2 (Baseline/Day 0)

A randomization number will be assigned within one day after the screening visit (subject eligibility will be notified by phone), and the following assessments will be performed.

#### 1) Confirmation of Concomitant Medications

- Concomitant medications and any changes since the last visit will be confirmed.

#### 2) Confirmation of Adverse Events

- The investigator must record all adverse events that occur during the clinical trial. The investigator will assess the adverse event and record the name of the event, onset date, resolution date, severity, causality, actions taken, and outcome.

## 3) Vital Signs Measurement

- Vital signs including blood pressure (systolic, diastolic), pulse rate, and body temperature will be measured. Blood pressure and pulse rate will be measured using an automated sphygmomanometer while the subject is seated after resting for at least 3 minutes at every visit. Body temperature will be measured using an electronic thermometer after blood pressure is measured.

## 4) Assessments of WURSS-21-K, Nasal Symptom Score VAS, Systemic Symptom Score VAS, EQ-5D-5L

## 5) Assignment of Randomization Number

- Subjects who are deemed eligible for this clinical trial based on the inclusion/exclusion criteria will be assigned a randomization number in the following format, in the order of their enrollment.
- Site codes: Daejeon University Daejeon Korean Medicine Hospital 01, Kyung Hee University Korean Medicine Hospital 02, Pusan National University Korean Medicine Hospital 03

|                              |
|------------------------------|
| ✓ KIOM_2024_CC_GGTCS_0X_R000 |
|------------------------------|

## 6) Prescription and Dispensing of Investigational Products

- A 7-day supply of the investigational product will be prescribed and dispensed for consumption until the next visit. Subjects will be instructed on the dosage, administration, precautions, and how to return any remaining investigational products to prevent loss or overdose. They will also be encouraged to return empty packets if possible.

## 7) Distribution and Instruction on Cold Diary

- Subjects will be given a cold diary to be completed until the next visit and will be trained to record their WURSS-21-K, Nasal Congestion Severity Score, Nasal Symptom Score VAS, Systemic Symptom Score VAS, and duration of cold symptoms daily.

## 8) Instruction on Next Visit Schedule

- Subjects will be instructed on the schedule for their next visit.

**10.2.3. Visit 3(Final visit/Day 7-10)**

## 1) Confirmation of Concomitant Medications

- Concomitant medications and any changes since the last visit will be confirmed.

## 2) Confirmation of Adverse Events

- The investigator must record all adverse events that occur during the clinical trial. The investigator will assess the adverse event and record the name of the event, onset date, resolution date, severity, causality, actions taken, and outcome.
- 3) Vital Signs Measurement
- Vital signs including blood pressure (systolic, diastolic), pulse rate, and body temperature will be measured. Blood pressure and pulse rate will be measured using an automated sphygmomanometer while the subject is seated after resting for at least 3 minutes at every visit. Body temperature will be measured using an electronic thermometer after blood pressure is measured.
- 4) Assessments of WURSS-21-K, Nasal Congestion Severity Score, Nasal Symptom Score VAS, Systemic Symptom Score VAS, Global Evaluation of Efficacy, EQ-5D-5L, and duration of cold symptoms.
- 5) Laboratory Test
- Subjects will undergo laboratory tests.
    - ✓ Complete blood count: RBC, WBC, Hemoglobin, Hematocrit
    - ✓ Liver function test: AST, ALT, BUN, Creatinine
  - The investigator may conduct additional tests related to any abnormal results.
- 6) Return of Investigational Products and Compliance Test
- Subjects must return any investigational products remaining from the last 7 days. The pharmacist will check the quantity of returned products, document the medication administration to confirm that each subject took the correct dose, and verify that the investigational product inventory matches the usage records.
- 7) Cold Diary Check
- The cold diary distributed at Visit 2 will be checked to ensure it has been properly completed.

#### **10.2.4. Additional Visits**

Additional visits can be made as needed at the subject's request or at the discretion of the investigator. During an additional visit, concomitant medications and adverse events will be checked, vital signs will be measured, and laboratory tests may be conducted at the investigator's discretion.

#### **10.2.5. Monitoring for Symptom Worsening**

If a subject's symptoms worsen during a visit or between visits, medical examinations and actions will be

taken. For subjects with a possibility of rapid symptom worsening, their condition will be checked by phone within 3 days after the visit. If a high fever or extreme pain occurs, the use of a rescue medication (Acetaminophen) is permitted. If the investigator determines that a prohibited concomitant medication is necessary, the study will be discontinued for that subject and the required medication will be provided.

### **10.3. Outcome Measures**

#### **10.3.1. Primary Outcome Measures**

##### **10.3.1.1. Wisconsin Upper Respiratory Symptom Survey, Korean version (WURSS-21-K) Total Score**

- The WURSS-21 is a validated assessment tool for measuring the severity of common cold symptoms and quality of life. A study on the reliability and validity of the Korean version, WURSS-21-K, has been conducted.
- It consists of a total of 21 questions: one question about the overall feeling of illness, 10 questions about the severity of cold symptoms, 9 questions about quality of life, and one question to compare symptom improvement/worsening compared to the previous day.
- For the question on symptom improvement/worsening, subjects will choose one of seven options: "very much better," "somewhat better," "a little better," "about the same," "a little worse," "somewhat worse," or "very much worse."
- The other 20 questions are structured on a 0-7 Likert scale (0 = none at all, 1 = very little, 3 = a little, 5 = moderate, 7 = very).
- The total score, which is the sum of the scores for all 21 questions, will be calculated and evaluated.
- At Visit 2, a diary containing the WURSS-21-K will be distributed and subjects will be instructed to complete it daily by themselves. It will be collected at Visit 3.

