| Efficacy Outcome Measures          | 
 
• Primary Outcome Measures 
 
1. Change in the WURSS-21-K total score (symptom score + quality of life score) from Baseline to Day 7
 
 
 
• Secondary Outcome Measures 
 
1. Change in the WURSS-21-K total score (symptom score + quality of life score) from Baseline to each time point (excluding Day 7)
 
2. Change in the WURSS-21-K symptom score from Baseline to each time point
 
3. Change in the WURSS-21-K quality of life score from Baseline to each time point
 
4. Change in the Nasal Congestion Severity Score from Baseline to each time point
 
5. Change in the Nasal Symptom Score VAS from Baseline to each time point
 
6. Change in the Systemic Symptom Score VAS from Baseline to each time point
 
 
 
 |

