### • Statistical Analysis of Outcome Measures

1. Primary Outcome Measures: Change in WURSS-21-K Total Score (Symptom Score + Quality of Life Score) from Baseline to Day 7
  - Research Hypothesis: The change in the WURSS-21-K total score from baseline to Day 7 in the test group is not equal to the change in the WURSS-21-K total score from baseline to Day 7 in the control group.
  - The primary outcome measures will be analyzed using an ANCOVA model, with the groups as a fixed effect and the baseline WURSS-21-K total score as a covariate. If necessary, variables that show a statistical difference in demographic characteristics or variables that may affect cold symptoms can be included as covariates. The least-square mean (LSM) for the difference between the test group and the control group will be calculated, and the 95% confidence interval and p-value for this difference will be presented.

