10.3.2. Secondary Outcome Measures

10.3.2.1.WURSS-21-K Symptom Score

- This score is calculated by summing the scores of the 10 questions in the WURSS-21-K that evaluate symptoms.
- Daily diary containing the WURSS-21-K will be distributed at Visit 2, and subjects will be instructed to complete it daily. It will be collected at Visit 3.

10.3.2.2.WURSS-21-K Quality of Life Score

- This score is calculated by summing the scores of the 9 questions in the WURSS-21-K that evaluate quality of life.
- Daily diary containing the WURSS-21-K will be distributed at Visit 2, and subjects will be instructed to complete it daily. It will be collected at Visit 3.

10.3.2.3.Nasal Congestion Severity Score

WURSS-21-K 상기도 감염 설문 - 21 일과 증상 기록

날짜(연월일):  
년 월 일

시간:  
오전 : 오후

병호:

다음 각각의 항목에 대하여 동그라미안에 체크하세요:

|                    | 아프지
않다
0        | 아주
조금
1         | 조금
2 3             | 보통
4 5             | 매우
6 7             |
|--------------------|-----------------------|-----------------------|-----------------------|-----------------------|-----------------------|
| 오늘 얼마나 아프다고 느끼십니까? |  |  |  |  |  |

각각의 증상에 대해 지난 24시간 동안의 감기증상으로 힘들었던 정도를 평가해주세요:

|               | 이러한 증상
은 없었습니다
0 | 아주
조금
1         | 조금
2 3             | 보통
4 5             | 매우
6 7             |
|---------------|------------------------|-----------------------|-----------------------|-----------------------|-----------------------|
| 콧물            |   |  |  |  |  |
| 코막힘           |   |  |  |  |  |
| 재채기           |   |  |  |  |  |
| 목이 아픔         |   |  |  |  |  |
| 목이 간질거리는 느낌   |   |  |  |  |  |
| 기침            |   |  |  |  |  |

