## **11.2. Statistical Analysis of Outcome Measures**

### **11.2.1. Primary Outcome Measures**

Hypothesis: The mean change in the WURSS-21-K total score (symptom score + quality of life score) from baseline to Day 7 is not equal between the test group and the control group.

The analysis will be conducted using an ANCOVA model with the group as the effect and the baseline WURSS-21-K total score as a covariate. If necessary, other variables that show a statistical difference in demographic characteristics or that could affect cold symptoms will also be included as covariates. The least-square mean (LSM) difference between the control and test groups, its 95% confidence interval, and the p-value will be presented.

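### Section 10.3.1.1 sums all 21 WURSS-21-K questions for the primary total, but the synopsis and Section 11.2.1 use symptom plus quality-of-life scores (19 items), and the 21-question sum cannot be computed as written

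*Protocol*

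**What the plan says.** Three places define the primary total as a sum of two subscores:

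- Synopsis, efficacy outcome measures: "Change in the WURSS-21-K total score (symptom score + quality of life score) from Baseline to Day 7".
- Synopsis, statistical analysis: "Change in WURSS-21-K Total Score (Symptom Score + Quality of Life Score) from Baseline to Day 7".
- Section 11.2.1, the hypothesis: "The mean change in the WURSS-21-K total score (symptom score + quality of life score) from baseline to Day 7 is not equal" between the groups.

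Section 10.3.2 fixes the two subscores. For symptoms: "This score is calculated by summing the scores of the 10 questions in the WURSS-21-K that evaluate symptoms". For quality of life: "This score is calculated by summing the scores of the 9 questions in the WURSS-21-K that evaluate quality of life".

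Section 10.3.1.1, which describes how the primary score is built, gives a different rule: "The total score, which is the sum of the scores for all 21 questions, will be calculated and evaluated". The same section divides the instrument into one overall illness question, 10 symptom questions, 9 quality-of-life questions and "one question to compare symptom improvement/worsening compared to the previous day". It assigns a 0 to 7 rating to 20 of these. For the last question it lists seven verbal options and gives no numbers. The Korean form reproduced in Section 10.3.2 agrees: numbered columns for the other items, words only for the final one.

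**The concern.** Both rules are current text, both describe the primary endpoint, and they cannot both hold. A programmer working from 10.3.1.1 and a statistician working from 11.2.1 would produce different primary variables. The first would also have to invent codes and a direction for the last question.

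The discrepancy reaches beyond the primary test. The same total is the baseline covariate in the primary ANCOVA, the first secondary endpoint at the other time points, and the variable in the exploratory comparison by cold pattern. If the definition were settled only after results were visible, the primary result would depend on a choice made with the data in view.

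The last question is also a different kind of measurement. The other items rate how bad the cold is. This one rates how today compares with yesterday, so its answer need not track severity.

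**Working it through.** **Item counts and ranges** (Sections 10.3.1.1 and 10.3.2)

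- Whole instrument: 1 + 10 + 9 + 1 = 21 questions.
- Synopsis and 11.2.1: 10 + 9 = 19 items. Maximum 19 × 7 = 133, range 0 to 133.
- Section 10.3.1.1: all 21. The 20 rated items reach 20 × 7 = 140, plus one item without codes.
- Difference: 21 − 19 = 2 items. The overall illness item adds up to 7 points. The change item adds an undefined amount.

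The protocol gives no coding for the change item. Under three assumed codings the 21-question maximum would be 140 + 6 = 146 (0 to 6), 140 + 7 = 147 (1 to 7) or 140 + 3 = 143 (−3 to +3). The range is therefore not fixed by the text.

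**What the change item measures on Day 7**

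Assume a coding in which worse is higher, and take four subjects:

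- recovered on Day 5: no change since yesterday;
- still ill, static: no change since yesterday;
- still ill, improving: better;
- still ill, deteriorating: worse.

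The recovered subject scores the same as the static ill subject, worse than the improving one and better than the deteriorating one. Early recovery is foreseen: Section 9.1 has subjects stop treatment when symptoms disappear before Day 7, and Section 10.3.2.6 tracks resolution daily. Subtracting the baseline answer does not help, because it gives the difference between two one-day changes, not the change in severity over seven days.

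**Sample size** (Section 5.3: difference 10, SD 21, two-sided 5%, power 80%, 1:1 allocation, 20% dropout)

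- n per group = 2(z₀.₉₇₅ + z₀.₈₀)² × SD² / difference².
- With the rounded values printed: 2 × (1.96 + 0.84)² × 441 / 100 = 69.15. With unrounded z values: 69.227, the protocol's figure. Both round up to 70.
- Dropout: 70 / (1 − 0.20) = 87.5, rounded up to 88 per group, 176 in total.
- Power at 70 per group: 80.4%.

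The protocol's figures reproduce, and the item count does not enter the formula. What matters is whether 10 and 21 describe the total that will be analysed. Section 5.3 and its Table 1 name the instrument only. The pre-treatment means in Table 1 (54.74 to 66.48) lie well inside both 0 to 133 and 0 to 140, so they do not show which total was used.

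Illustration only, under assumed scaling by item count. If difference and SD scale together, n stays at 70. If the SD grows and the difference stays at 10:

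- SD 21 × 20/19 = 22.11 gives n = 77, with power at 70 per group of about 76%.
- SD 21 × 21/19 = 23.21 gives n = 85, with power at 70 per group of about 72%.

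These figures show why the source total should be checked. They do not predict a shortfall.

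**The case against.** The strongest reply is that the intended endpoint is clear. Every place that states the primary endpoint or its hypothesis with a definition gives the same one, and 10.3.1.1 is a single outlying sentence in the description of the instrument. Since that section gives numbers to only 20 questions, its rule cannot be followed literally and would probably be noticed. A statistical analysis plan or a diary scoring specification, neither of which is shown, may already settle the matter.

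This narrows the doubt but does not remove it. The outlying sentence stands in the section that specifies how the score is constructed, and no other text reconciles it. A later document that chose 19 items would still contradict it.

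A reader might infer three stronger claims, which the protocol does not support:

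- *That the change item could swing the result by most of the planned effect.* Coded 1 to 7 it spans 6 points against a planned difference of 10. But one subject's possible range on an item is not comparable with a difference between group means, and the coding is an assumption.
- *That the item systematically penalises faster recovery.* This holds against a subject who is still improving. It does not hold against one who is static or deteriorating. The mix of such subjects in each group is not given.
- *That the trial is wrongly sized.* The arithmetic reproduces, and nothing shows that the planning figures came from a different total.

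**Conclusion.** The contradiction stands and concerns the primary endpoint, so it needs correcting before unblinding. Two definitions are in force, of 19 and 21 questions. The first has a range of 0 to 133. The second cannot be computed as written, because one item has no numeric codes. That item is a transition rating: a recovered subject and an unchanged ill subject can give the same answer, so it should not be part of a severity total or its change from baseline. The overall illness item does not share this problem, since it is rated 0 to 7 in the same direction as severity, but it too lies outside the definition used in the endpoint and analysis sections.

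Including the change item could dilute a treatment effect. How much, and in which net direction, cannot be determined from the protocol. The planned 70 per group and 88 with dropout are not put in doubt. It remains open which total the difference of 10 and SD of 21 describe. The conclusion rests on the protocol alone and does not exclude that an unseen document already applies one rule.

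**What to change.** 1. First establish which total the Table 1 figures in Section 5.3 were based on, and state it there.
2. Then, before unblinding, replace the sentence in 10.3.1.1 that sums all 21 questions. The total should be the sum of the 10 symptom items and the 9 quality-of-life items, range 0 to 133, as the synopsis and 11.2.1 already imply.
3. State in the same place that the overall illness item and the change-since-yesterday item are reported separately and do not enter the total.
4. Align the diary scoring program with that item list.
5. If the planning figures turn out to come from a different total, restate the basis for the difference of 10 and SD of 21 on the 19-item score.

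The cost is a sentence or two in the protocol, a look at the source of the planning figures and a check of the scoring program. The diary and the data collected do not change.
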